### Study design

We plan a type 3 hybrid implementation-effectiveness trial [14], registered as NCT07141394 on 8/26/2025 and determined to be non-research by VA’s Central Institutional Review Board. We will use stratified block randomization, stratified by tertiles of each site’s number of HUD-VASH full-time equivalent (FTE) employees (proxy for size and resources).

Within the 12 sites, we will use a stepped wedge cluster randomized trial design [35] (Fig. 2) to study implementation outcomes, balanced for allocation to treatment timing and assignment to REP vs. REP + CE arms across 3 strata of 4 sites each (Fig. 3). Using a random number generator with assignment by our statistician, each stratum will be randomly assigned to 1 of 3 possible cohort pairings (cohorts 1 & 2; 2 & 3; 1 & 3). Within each stratum, 4 sites will be randomly assigned to 1 of the 2 cohorts in the pair, ensuring that there are early and late treatment timings within each stratum. Within each stratum-cohort combination (n = 2), the REP vs. REP + CE implementation strategy arm will be randomly assigned, and consent obtained thereafter. The staggering of sites into cohorts is necessary to provide HUD-VASH sites with optimal EBP and CE training within our resources. We selected the 9-month duration of REP, before augmenting with 9 months of CE at REP + CE sites, because we found this duration of REP to be effective in prior trials of a psychosocial EBP for HEVs [36]. We will be unable to blind sites (clusters) assigned to CE augmentation, as we need to engage with leadership regarding peer supports’ commitments. To optimize power in our effectiveness analyses, we will compare sites that receive REP vs. REP + CE vs. all other HUD-VASH sites in the nation that are not engaged in CARE-VASH.

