#### MAT and CBT-SUD reach, adoption, and sustainment

Table 3 lists measures for reach, adoption, and sustainment. Measures of reach for MAT indicate one prescription (30–90 days/duration) and use of MAT for 180 days [40]. For CBT-SUD, reach assesses a single visit and a threshold of 9 visits (which may equate to meaningful impacts in substance use/functioning) [41]. We will use VA administrative data to abstract these measures for HEVs in HUD-VASH at implementation sites. Sustainment will reflect these reach and adoption measures after our intensive implementation supports end (cross-sectionally at 9 months after we end each implementation cohort).

**Table 3 Tab3:** Reach, adoption, and sustainment measures

	**MAT**	**CBT-SUD**
Reach^*^	• % HEVs who used MOUD for OUD, ≥ 1 prescription • % HEVs who used MOUD for OUD for 180 days since initial prescription (without a break ≥ 14 days in supply) • % HEVs who used MAUD for AUD, ≥ 1 prescription • % HEVs who used MAUD for AUD for 180 days since initial prescription (without a break ≥ 14 days in supply)	• % HEVs with SUD with ≥ 1 CBT-SUD visit • % HEVs with SUD with ≥ 9 CBT-SUD visits
Adoption^*^	• % HUD-VASH and mental health prescribers engaged with HEVs^**^ who ordered MOUD/MAUD at least once in the Electronic Health Record	• % HUD-VASH case managers who delivered ≥ 1 CBT-SUD session
Sustainment^¶^	• Reach and adoption measures described above	Reach and adoption measures described above

^*^Reach and adoption measures will be assessed at 18 months post-implementation

^**^Mental health prescribers engaged with HEVs will be defined as prescribers listed on AD dashboards, i.e., most recent mental health prescriber for Veterans who had ≥ 2 billable HUD-VASH encounters in the past year (§B3bi)

^¶^Sustainment will be assessed 9 months after we conclude REP vs. REP + CE for each cohort. HEVs referenced in this table include HEVs enrolled in HUD-VASH at implementation sites

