We will use a staggered adoption model [42], comparing reach and adoption pre-CARE-VASH, to REP alone, and to REP + CE. These models utilize fixed effects for sites to account for time-invariant confounders between sites as well as fixed effects for time-period to account for secular trends. We will implement this approach [42] using a doubly robust estimator based on stabilized inverse probability weighting [43], with weights based on HEV demographics and comorbidities (using the Multimorbidity-Weighted Index) [44]. The average treatment effect on the treated will be estimated based on comparison to the not-yet-treated periods and presented using an event-study approach which will estimate the intervention effect across time (i.e., for each quarter-year). In addition to providing intervention estimates for each quarter-year of the study, a pooled intervention effect estimate will be aggregated across the study period by taking weighted averages of the event-study estimates with non-parametric bootstrapping (1000 replications) used to provide standard errors for aggregated estimates. Sustainment will be compared between sites that received REP vs. REP + CE, with reach and adoption measures adjusted as described.

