##### Budget impact analysis

We will also prepare a budget impact analysis (Table 4), characterizing the costs, cost offsets, and non-financial benefits of: MAT and CBT-SUD sustainment and spread in HUD-VASH; and REP vs. REP + CE. We will compare healthcare utilization costs between REP and REP + CE sites using a difference-in-differences research design. This will be performed using both the standard two-way fixed effect approach as well as with the Callaway and Sant’Anna [42] estimator, which takes into account staggered adoption. Our cost analyses will provide data about the magnitude and features of expected EBP costs and benefits. We will assess whether REP + CE yields a sufficient combination of downstream financial cost offsets and non-financial benefits to justify REP + CE vs. REP alone in spreading and sustaining MAT and CBT-SUD. We will also provide information about HUD-VASH site-level contextual factors that may signal an above-average benefit from using REP + CE (vs. REP alone).

**Table 4 Tab4:** Budget impact analysis

Expected resources (costs)		Expected benefits
**Implementation Strategy Costs**	**Care delivery costs**	**Cost offsets and non-financial benefits**
• *Fixed*: Implementation team, HUD-VASH and mental health staff time spent in EBP training • *Variable*: Staff time spent giving/receiving AD and/or CBT-SUD TA, implementation team time spent consulting with HUD-VASH peers, peer time spent delivering CE*	• HUD-VASH and mental health prescriber time spent delivering MAT • HUD-VASH staff time spent delivering CBT-SUD • Downstream healthcare use	• *Cost offset:* decreased use of VA housing services • *Non-financial benefits*: HEVs’ housing stability; improved HEVs’ care experiences; improved HUD-VASH team experiences providing care

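### Against pre-CARE-VASH, the not-yet-treated comparison gives no reach or adoption effect for cohort 3, or for any cohort once cohort 3 has launched

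*Protocol article*

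**What the plan says.** The section on MAT and CBT-SUD reach, adoption, and sustainment sets the analysis: "We will use a staggered adoption model [42], comparing reach and adoption pre-CARE-VASH, to REP alone, and to REP + CE". The model has site fixed effects and "fixed effects for time-period to account for secular trends". The comparator is given as "The average treatment effect on the treated will be estimated based on comparison to the not-yet-treated periods". The section on budget impact analysis ties the same reference to the Callaway and Sant'Anna "estimator, which takes into account staggered adoption". The reach section also promises an intervention estimate for each quarter-year of the study and one pooled effect over the study period.

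The data for this model are limited to the trial's own sites: "We will use VA administrative data to abstract these measures for HEVs in HUD-VASH at implementation sites". The Study design section agrees: "Within the 12 sites, we will use a stepped wedge cluster randomized trial design". The abstract's Methods say that REP goes to all 12 sites for 18 months, with CE added in six of them after month 9. The Table 3 footnote fixes the time point: "Reach and adoption measures will be assessed at 18 months post-implementation".

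An outside comparison group does exist in the plan, namely "all other HUD-VASH sites in the nation that are not engaged in CARE-VASH", but the Study design section assigns it to the effectiveness analyses. It reappears only under housing stability and acute care use.

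**The concern.** A not-yet-treated comparison needs at least one site that has not started. Here every site starts, so the last cohort to start never has a control, and the earlier cohorts lose theirs on the day it starts. After that date a period effect and a treatment effect cannot be told apart without a further assumption.

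This matters because the contrast with pre-CARE-VASH is the one that the reach section describes and the one that the section on sample size and power uses for its detectable differences. For that contrast, the article promises results for quarters and sites that the stated method cannot supply.

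**Working it through.** **1. The plan's own figures.** Inputs from the section on sample size and power: 7908 HEVs; AUD 53% at 9.9%; OUD 16% at 19.9%; CBT-SUD eligible 66% at 0.5%; two-sided alpha 0.05; power 80%. The figures are closest to a plain two-proportion calculation with 6 sites' worth of HEVs on each side and no inflation for clustering:

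n per side = [1.96·√(2p̄(1−p̄)) + 0.84·√(p₁(1−p₁) + p₂(1−p₂))]² / (p₂−p₁)²

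| Measure | Eligible | n per side (half) | Detectable, computed | Stated |
|---|---|---|---|---|
| MAUD | 4191 | 2096 | 2.74 points | 2.7 |
| MOUD | 1265 | 633 | 6.65 points | 6.6 |
| CBT-SUD | 5219 | 2610 | 0.71 points (0.77 with continuity correction) | 0.8 |

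MAUD and MOUD reproduce. CBT-SUD rounds to 0.8 only with the continuity correction. The stated figures therefore use the HEVs of all 12 sites.

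**2. What is identified.** Assumptions: three cohorts of 4 sites, 2 of them REP + CE (from the per-cohort and per-site interview counts under HUD-VASH staff semi-structured interviews); 18 months per cohort; equal spacing of s months. Spacing is not in the text and Fig. 2 is not shown, so s is varied. A cohort is identified only until cohort 3 launches:

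- Cohort 1: min(18, 2s) months = c₁
- Cohort 2: min(18, s) months = c₂
- Cohort 3: 0 months

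Identified post-launch site-months = 4(c₁ + c₂), out of 12 × 18 = 216. Identified CE site-months (months 10 to 18), for REP + CE versus pre-CARE-VASH, = 2[max(0, c₁−9) + max(0, c₂−9)], out of 6 × 9 = 54.

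| s (months) | c₁, c₂ | Post-launch site-months | CE site-months |
|---|---|---|---|
| 3 | 6, 3 | 36/216 = 17% | 0/54 = 0% |
| 6 | 12, 6 | 72/216 = 33% | 6/54 = 11% |
| 9 | 18, 9 | 108/216 = 50% | 18/54 = 33% |
| 12 | 18, 12 | 120/216 = 56% | 24/54 = 44% |
| 18 | 18, 18 | 144/216 = 67% | 36/54 = 67% |

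Beyond 18 months the shares do not rise. The 18-month value is identified for no cohort if s < 9, for cohort 1 only if 9 ≤ s < 18, for cohorts 1 and 2 if s ≥ 18, and never for cohort 3.

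**3. Independent check.** A rank test was run on a model with cohort effects, quarter effects and a separate effect for every treated cohort-quarter. Of 18 implementation cohort-quarters, 3, 6, 9, 10 and 12 are estimable at gaps of 3, 6, 9, 12 and 18 months. Cohort 3 contributes none at any gap, and no cell at or after its launch is estimable.

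**4. The concurrent CE contrast.** The rank test was repeated with a separate CE increment in REP + CE sites, at gaps of 3, 6 and 9 months. All 9 CE-phase cohort-quarters are estimable each time, 3 of them in cohort 3.

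**5. Effect on the stated detectable differences.** Cohorts 1 and 2 hold 8 sites, 4 per arm. Replacing half of the eligible HEVs by one third (1397, 422 and 1740 per side) in the formula of step 1 gives detectable increases of 3.39, 8.23 and 0.93 points. Power at the stated 2.7, 6.6 and 0.8 points becomes 0.62, 0.62 and 0.71, against 0.79, 0.795 and 0.865 from the same formula with all 12 sites.

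**The case against.** Four points can fairly be made on the other side.

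- **The trial's declared question is REP + CE versus REP.** This stands. A reader might infer that cohort 3 yields no effect estimate of any kind. The documents do not support that: REP-only sites never receive CE, so the randomised contrast within cohort is available in all three cohorts. For the CE step, the article's Discussion also speaks of within-site analyses that starting with REP alone makes possible. What fails is the contrast with pre-CARE-VASH.
- **A pooled effect can still be formed.** This also stands. If the event study runs on time since launch, cohort 1 supplies all six quarters once spacing is 9 months or more, and the weighted average exists. It is an average over cohorts 1 and 2 only. Estimates for every calendar quarter of the study fail at any spacing.
- **Start date is randomised.** Losing cohort 3 therefore costs coverage and precision and does not by itself bias the estimate from cohorts 1 and 2. A reader might infer that the final package goes unevaluated because packages are refined along the way. The article does not say how much they change between cohorts, so that cannot be claimed.
- **Not-yet-treated periods might mean each site's own baseline.** This does not rescue the plan. A pure before-after contrast gives up the secular-trend adjustment that the same paragraph claims. An ordinary two-way fixed-effects fit returns late values only by restricting how effects vary over time or cohort. Neither is the stated comparison.

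Lack of a control after the last step is inherent when all sites cross over, but it then has to limit what is promised. An article may condense, yet here the comparator, the data source and the promised outputs are all stated and do not fit together.

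**Conclusion.** The point holds for the effects of REP and REP + CE versus pre-CARE-VASH on reach and adoption. Under the stated comparison, cohort 3 (4 of 12 sites, 2 of the 6 REP + CE sites) contributes no such effect, and cohorts 1 and 2 stop contributing when cohort 3 launches. That conclusion does not depend on spacing.

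The size of the loss does depend on it. Between 17% (3 months) and at most 67% (18 months or more) of post-launch site-months are identified, and between 0% and 67% of CE site-months for REP + CE versus pre-CARE-VASH. These ranges assume equal spacing and 4 sites per cohort.

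The detectable differences rest on 12 sites where at most 8 can contribute. On the article's apparent formula they rise to about 3.4, 8.2 and 0.9 points. These figures carry over that formula's lack of clustering inflation and treat the 8 sites as contributing in full, so they show direction and rough scale only. The randomised REP + CE versus REP contrast within cohort is not affected.

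**What to change.** **Preferred, for reach.** Add the non-CARE-VASH HUD-VASH sites to the staggered-adoption model as never-treated controls. Keep all 12 sites and all six post-launch quarters. State the parallel-trends assumption and show the pre-launch quarters. The Background reports MAT and CBT-SUD receipt from a prior HUD-VASH evaluation of 63,939 HEVs, and these outside sites already serve the housing and acute care analyses. The cost is a wider extraction and some analysis wording. The downside is that these controls are not randomised.

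**For adoption.** Do the same only if the denominators can be extracted at those sites. The prescriber list depends on dashboards still to be adapted for HUD-VASH, and the article does not show that the case-manager measure is available outside the 12 sites.

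**Otherwise.** State that effects versus pre-CARE-VASH apply to cohorts 1 and 2 before cohort 3's launch. Drop the promise of an estimate for every quarter-year of the study, and restate the detectable differences on that basis. This costs only wording and a recalculation.

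**In either case.** Define the CE increment separately, as the concurrent REP + CE versus REP contrast within cohort, using all 12 sites.

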#### Sample size and power

Across the 12 sites, we will have 7908 HEVs undergoing REP or REP + CE. For assessing reach, we will examine the proportion of eligible HEVs who receive MAT and the proportion of eligible HEVs who receive CBT-SUD. Among HUD-VASH Veterans with AUD (53%) and OUD (16%), ~ 9.9% and 19.9% currently receive MAT, respectively. Over half (66%) are eligible for CBT-SUD, though only 0.5% receive it. We can approximate the power of our staggered adoption model approach to compare REP alone (or REP + CE) to pre-CARE-VASH based on the power to detect a difference in proportion assuming a within-site correlation of outcomes over time of rho = 0.04. With this sample size using a two-sided alpha level of 0.05, we would have 80% power to minimally detect an absolute increase in reach for MAUD of 2.7 percentage points, MOUD of 6.6 percentage points, and CBT-SUD of 0.8 percentage points. These minimally detectable estimates are much smaller than those found for a MAUD implementation effort [45] and an MOUD implementation study [46]. Though a systematic review of CBT implementation studies note that the implementation evaluations did not address changes in reach [47], we can extrapolate from MAT studies to estimate that concerted implementation efforts would achieve an increase in CBT-SUD’s reach of > 0.8 percentage points.

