In our prior evaluation [10] for HEVs who attained HUD-VASH housing from 2018–2021 (n = 63,939), most had ≥ 1 SUD (66%, n = 42,182). Veterans with SUDs were 1.4 times more likely to have a negative exit from HUD-VASH within one year of move-in. Though nearly half (47.3%, n = 19,931) of HEVs with SUDs in HUD-VASH had ≥ 1 SUD specialty visit, receipt of EBPs for SUDs was low. In the year after HUD-VASH move-in, only 9.6% and 19.9% of Veterans with alcohol use disorder (AUD) and opioid use disorder (OUD), respectively, received ≥ 1 medication for addiction treatment (MAT) prescription [11]. This finding is concordant with a prior study of OUD in VA homeless programs, which describes gaps in MAT provision and asserts the importance of policy goals for addressing OUD among HEVs [12]. Moreover, among HEVs with stimulant use disorder (35.9% of HUD-VASH participants), < 0.5% received Cognitive Behavioral Therapy for SUDs (CBT-SUD) [10]. Therein, though the VA has implemented MAT and CBT-SUD within mental health clinics, HUD-VASH adoption is low. National implementation of evidence-based practices (EBPs) for SUDs within HUD-VASH can improve housing outcomes among homeless-experienced Veterans.

This paper describes the Coordinated Access for Addiction Recovery and Equity in VA Supportive Housing (CARE-VASH) Quality Enhancement Research Initiative (QUERI), which will implement MAT and CBT-SUD at 12 HUD-VASH sites and compare the impacts of two implementation strategies on implementation and effectiveness outcomes. To implement and sustain MAT and CBT-SUD across sites, we will use the Replicating Effective Programs (REP) bundle for 18 months, engaging diverse stakeholders (“Learning Community”) to package the EBPs; provide staff training; conduct evaluation; and support maintenance [13]. In addition to REP, 6 sites will receive 9 months of Consumer Engagement (CE). In CE, Veterans will be activated to use EBPs via a Veteran panel, educational materials, and HUD-VASH peer coaching.

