### Participating sites

We identified 12 geographically diverse HUD-VASH implementation sites; each is nested in a division of a VA healthcare system and is comprised of ≥ 1 HUD-VASH team. Collectively, these sites serve ~7908 HEVs/year. Each site will implement MAT and CBT-SUD. Of note, our sample size (12 sites) was pre-determined by our funder.

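### The detectable increases in reach (2.7 / 6.6 / 0.8 points) are close to those for independent Veterans and overstate power under the planned model, above all for REP + CE versus pre-CARE-VASH

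*Protocol article*

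**What the plan says.** The section Sample size and power starts from the total: "Across the 12 sites, we will have 7908 HEVs undergoing REP or REP + CE". It then gives the eligible shares and current reach: "Among HUD-VASH Veterans with AUD (53%) and OUD (16%), ~ 9.9% and 19.9% currently receive MAT, respectively", and for CBT-SUD "Over half (66%) are eligible for CBT-SUD, though only 0.5% receive it". The power of the staggered adoption model, for REP alone (or REP + CE) against the pre-CARE-VASH period, is approximated by the "power to detect a difference in proportion assuming a within-site correlation of outcomes over time of rho = 0.04". The result, "using a two-sided alpha level of 0.05", is 80% power for an "absolute increase in reach for MAUD of 2.7 percentage points, MOUD of 6.6 percentage points, and CBT-SUD of 0.8 percentage points". One set of three figures serves both REP alone and REP + CE. The section goes on to say that these values lie well below the effects seen in earlier MAUD and MOUD implementation work.

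The section MAT and CBT-SUD reach, adoption, and sustainment describes the model being approximated: fixed effects for site and for time period, with treated periods compared with not-yet-treated ones. The section Participating sites adds that "our sample size (12 sites) was pre-determined by our funder". No detectable difference is given for REP + CE versus REP.

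**The concern.** A reader who sees rho = 0.04 will assume that the grouping of Veterans in 12 sites has been allowed for. If the figures are really those of unclustered individuals, that assumption is wrong. The planned model has to separate the intervention effect from period effects, and a site's reach may drift between periods for reasons unrelated to the intervention. The two named contrasts also rest on different amounts of information: all 12 sites pass through 9 months of REP alone, but only 6 receive CE.

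The number of sites is fixed, so the detectable difference is what readers will use to interpret an inconclusive result. If it is too optimistic, a null finding will look like evidence of no effect.

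**Working it through.** **Inputs from the article.** 7908 Veterans; eligible 53% / 16% / 66%; baseline reach 9.9% / 19.9% / 0.5%; two-sided alpha 0.05; power 80%; 12 sites in 3 cohorts; 6 sites with CE after 9 months of REP. The order throughout is MAUD / MOUD / CBT-SUD.

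**Step 1: reproduce the stated figures.** Eligible: 7908 × 0.53 / 0.16 / 0.66 = 4191 / 1265 / 5219. Half per group: n = 2096 / 633 / 2610. Solve d = (1.96 + 0.8416) × √[(p₁q₁ + p₂q₂)/n] with p₂ = p₁ + d:

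- MAUD: 2.8016 × √[(0.0892 + 0.1104)/2096] = 2.73 points (stated 2.7)
- MOUD: 2.8016 × √[(0.1594 + 0.1949)/633] = 6.63 points (stated 6.6)
- CBT-SUD: 2.8016 × √[(0.00498 + 0.01200)/2610] = 0.71 points (stated 0.8)

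MAUD and MOUD match to rounding. CBT-SUD matches only approximately: a continuity correction gives 0.76, but then the other two become 2.79 and 6.81. The Background gives a slightly different MAUD baseline ("only 9.6% and 19.9% of Veterans with alcohol use disorder (AUD) and opioid use disorder (OUD), respectively"); using 9.6% gives 2.70, a negligible change.

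**Step 2: look for rho.** Used as a pre-post correlation, rho multiplies the variance by 1 − 0.04 = 0.96 and gives 2.68 / 6.49 / 0.70. That is almost the same as independence.

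**Step 3: a layout closer to the planned model.** The article does not give this layout, so all of it is assumed:

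- Five 9-month blocks, with block 1 as baseline for all sites; four sites start REP in each of blocks 2, 3 and 4.
- After one REP block, half of each cohort moves to REP + CE and the other half stays on REP for one more block. Later blocks are left out.
- m = eligible/12 = 349 / 105 / 435 Veterans per site and block; equal sites; period effects; ICC 0.04.
- The variance of a site-block mean is w × [ICC + (1 − ICC)/m]. The covariance of two blocks of one site is w × ICC × CAC, where CAC is the between-period site autocorrelation. Here w = p̄(1 − p̄), with p̄ midway between baseline and baseline plus the stated increase.
- Generalised least squares gives a variance w × v for each contrast; the detectable difference is 2.8016 × √(w × v).

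Example, MOUD, REP + CE versus pre, CAC 1: w = 0.232 × 0.768 = 0.1782 and v = 0.00636, so 2.8016 × √0.001133 = 9.4 points.

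| Contrast | CAC 1 (stable sites) | CAC 0.9 |
|---|---|---|
| REP vs pre | 2.7 / 6.5 / 0.7 | 4.2 / 7.7 / 1.2 |
| REP + CE vs pre | 4.0 / 9.4 / 1.1 | 6.1 / 11.1 / 1.8 |
| Stated for both | 2.7 / 6.6 / 0.8 | 2.7 / 6.6 / 0.8 |

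For MOUD with stable sites, the variance for REP + CE is (9.4/6.5)² ≈ 2.1 times that for REP.

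**Step 4: power at the stated differences.** Power = Φ(2.8016 × stated/detectable − 1.96). For REP + CE versus pre with stable sites, unrounded values give about 48% / 50% / 56%. For MOUD: 2.8016 × 6.6/9.43 − 1.96 ≈ 0, hence 50%.

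**Step 5: a more favourable alternative.** A simple pre-post contrast over all 12 sites without period effects has variance (p₁q₁ + p₂q₂) × [(1 − ICC)/m + ICC(1 − CAC)]/12. At CAC 0.9 it gives 3.0 / 5.5 / 0.9 points.

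**The case against.** The strongest defence is that the powered contrast is with each site's own past. The article defines rho as a correlation over time within a site, and the model has site fixed effects. A constant site difference then cancels, and positive correlation does not inflate the variance. This stands. A reader might infer that rho should enter as a between-site design effect, 1 + (m − 1) × 0.04 = 14.9 / 5.2 / 18.4. The documents do not support that, because such a factor belongs to a parallel comparison between sites, which this section does not power.

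Three further points also stand in part:

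- **The match is not unique.** The assumed layout with stable sites gives 2.7 / 6.5 / 0.7 for REP versus pre, about as close as the independent test. For that contrast it cannot be said that period effects were ignored. CBT-SUD is not reproduced exactly by either route.
- **All 12 sites contribute to REP versus pre.** Without period effects the stated MOUD figure would even be conservative (5.5 at CAC 0.9), and MAUD and CBT-SUD would be within 0.3 points.
- **The article calls its method an approximation.** As a condensed text it may leave formulae and group sizes to a fuller document.

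None of this rescues the single set of figures for REP + CE. In the same layout that agrees with the stated values for REP, REP + CE needs clearly larger increases, even with no site drift at all.

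**Conclusion.** The point holds in a limited form. The stated figures are essentially those of independent Veterans split into two halves, and rho = 0.04 has no visible effect on them. For REP alone versus pre, they are attainable in the assumed stepped layout only if site reach is perfectly stable apart from the intervention and common period effects, a condition that the article does not state. For REP + CE versus pre, 80% power would need about 4.0 / 9.4 / 1.1 points in that best case and 6.1 / 11.1 / 1.8 at autocorrelation 0.9.

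These sizes rest on the assumed layout, an ICC of 0.04, equal sites and normal quantiles, so they illustrate the range and are not replacement values. Reading the stated figures as power for the randomised REP + CE versus REP comparison would go further than the article, which gives none for it. Nor can the sentence about earlier implementation studies be called wrong, because their effect sizes are not shown; it needs rechecking. This should be fixed, but it does not undermine the design.

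**What to change.** - Recompute the detectable differences from the planned design: 12 sites, 3 cohorts, period effects, a stated ICC, a range of between-period autocorrelation such as 0.8 to 1.0, and site-based degrees of freedom.
- Say what rho = 0.04 measures and how it enters the calculation.
- Report REP versus pre and REP + CE versus pre separately, and add the randomised REP + CE versus REP contrast.
- Replace 2.7 / 6.6 / 0.8 with the resulting range, and recheck against it the comparison with earlier studies and the extrapolation to CBT-SUD.

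The cost is one recalculation and a reworded paragraph. The number of sites, the allocation and the estimator stay as they are. The drawback is that the published figures will look less favourable, most of all for REP + CE.
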